## Abstract

**Background:**

Domperidone, a drug that enhances upper gastric motility, is an anti-dopaminergic medication that also elevates prolactin levels. It has been shown to safely increase the milk supply of lactating women. To date, researchers have analyzed the effects of domperidone on lactating woman with respect to the quantity of their milk production, adverse effects, and drug levels in the breast milk. However, the effect of domperidone on the macronutrient composition of breast milk has not been studied and current guidelines for fortification of human milk for premature infants do not distinguish between those women using or those not using domperidone. The purpose of this study is to evaluate the effect of domperidone (given to lactating mothers of very preterm infants) on the macronutrient composition of breast milk.

**Methods/Design:**

Mothers of infants delivered at less than 31 weeks gestation, who are at least 3 weeks postpartum, and experiencing lactational failure despite non-pharmacological interventions, will be randomized to receive domperidone (10 mg three times daily) or placebo for a 14-day period.

Breast milk samples will be obtained the day prior to beginning treatment and on days 4, 7 and 14. The macronutrient (protein, fat, carbohydrate and energy) and macromineral content (calcium, phosphorus and sodium) will be analyzed and compared between the two groups. Additional outcome measures will include milk volumes, serum prolactin levels (measured on days 0, 4, and 10), daily infant weights and breastfeeding rates at 2 weeks post study completion and at discharge. Forty-four participants will be recruited into the study. Analysis will be carried out using the intention to treat approach.

**Discussion:**

If domperidone causes significant changes to the nutrient content of breast milk, an alteration in feeding practices for preterm infants may need to be made in order to optimize growth, nutrition and neurodevelopment outcomes.

## Background

During the past two decades, significant advances in medical technology have contributed to the increased survival of preterm, very low birth weight infants. As mortality rates have declined, the focus has shifted to decreasing morbidity and length of hospital stay for these high-risk infants. Nutritional care is one area with great potential for improvement. There continue to be many unanswered questions as to what constitutes optimal nutrient intake for the extremely preterm neonate. Although the current literature states that fortified human breast milk is most desirable [1-6], the optimal macronutrient composition of prepared fortifiers continues to be studied [7]. Also, the shift from formula feeding of preterm infants to human breast milk has caused an increase in mothers of preterm infants providing expressed breast to their babies over prolonged periods.

Many mothers of very preterm infants experience difficulty maintaining milk production over several months, and hence medications such as domperidone are often recommended to help augment milk supply. Such medications increase maternal prolactin levels and have been shown to significantly increase the quantity of breast milk a lactating woman produces [8-18]. Higher prolactin levels have been linked to accelerated decline in protein levels in term breast milk [19,21]. However, there is a paucity of information in the literature, on the effect of domperidone on the macronutrient content of breast milk. Although pharmacological augmentation of breast milk volume is valuable, carefully conducted quantitative studies are required to assess the effect of such medication on human breast milk composition including protein, fat and other constituents. We, therefore, designed a study to determine the effect of domperidone on the macronutrient (protein, fat, and energy) and macromineral (calcium, phosphorus, and sodium) content of breast milk among mothers of very preterm infants.

## Summary of literature review

### a. Advantages of human breast milk

Breast milk is generally considered to be the optimal form of nutrition for all infants regardless of gestational age [1,2]. Preterm infants have better outcomes if they receive human breast milk during the first months after birth. Human breast milk provides both nutritive and nonnutritive benefits to preterm infants. Nutritive benefits include a whey predominant protein source, which is more easily digested and promotes more rapid gastric emptying. Human milk is also a source of the very long chain fatty acids, which are important components of brain and red cell membranes. Nonnutritive advantages include psychological benefits of maternal-infant bonding, improved gastrointestinal outcomes, reduced risk of atopic eczema, and fewer systemic infections during initial hospitalization, [3-7,24-28] as well as, improved psychomotor development [26-29].

### b. Expressed breast milk

Increasingly, mothers of premature babies being cared for in neonatal intensive care units are asked to provide expressed human breast milk for their babies. Most mothers express a strong desire to provide breast milk for their infant and verbalize positive feelings about being able to do something to help their ill baby. However, many mothers of very preterm infants find it difficult to provide adequate amounts of expressed breast milk to meet their baby's needs over prolonged periods of time. Stress related to the hospitalization, concerns related to the increased risk of mortality and morbidity, separation, and lack of infant suckling may contribute to decreased milk production [33]. Decreased milk production among mothers of very preterm infants expressing breast milk can occur as early as two weeks postpartum, although such problems typically peak between four and six weeks postpartum [8,33].

### c. Physiology of lactation

The initiation of lactation (lactogenesis) is a natural process that is based on a complex interaction of hormones. Changes in estrogen and progesterone during pregnancy alter the morphologic structure of breast tissue. Increasing levels of the hormone prolactin is key in the initiation and maintenance of lactation [34,35] and may play a role in the control of electrolyte composition [20,21] and alteration in amino acid concentration [19] of mature human breast milk. A significant increase in lactogenesis occurs following delivery with the concurrent decline in estrogen and progesterone. In addition, the tactile stimulus by the suckling baby causes a release of prolactin from the pituitary, which stimulates milk flow. This suckling induced prolactin release is a reflex related to hypothalamic serotoninergic neuron activation, accompanied by a concomitant increase of dopamine turn over [34,35]. Babies delivered at less than 32 weeks gestation are not able to effectively coordinate sucking, swallowing and breathing [36]. The lack of effective suckling that is associated with the delivery of a preterm baby as well as maternal stress, infection, or fatigue can lead to difficulties maintaining lactation [8,33].

### d. Non-pharmacological interventions to enhance human breast milk production

Non pharmacological measures such as added emotional support, kangaroo care/skin to skin, compressing and massage, relaxation techniques, expressing breast milk at the baby's bedside, increasing pumping times, and alterations in mechanical expression contribute to a variable level of success in augmenting milk production [9,37]. For those mothers whose milk production is refractory to non-pharmacological interventions, and who verbalize a continued desire to provide expressed breast milk, the use of pharmacological intervention may be recommended.

### e. Pharmacological interventions

The administration of an anti-dopaminergic drug, such as metoclopramide or domperidone has been shown to yield positive results. Endogenous dopamine has a physiological inhibitory role in the control of prolactin release. Therefore, the administration of a dopamine inhibitor increases plasma prolactin levels and induces lactogenesis [9]. Metoclopramide, a central dopamine antagonist, has been most widely studied and proven to be highly efficacious in augmenting milk supply [8,10-14]. However, reports indicate that it crosses the blood brain barrier, and is secreted in significant amounts in the breast milk [12]. As well, animal studies have reported dopamine mediated responses in the offspring of nursing rats [38].

### f. Why choose domperidone?

Both metaclopramide and domperidone are anti-dopaminergic drugs. Both induce lactation by inhibiting endogenous dopamine and thereby increasing plasma prolactin levels. Domperidone is a newly developed anti-emetic with no structural relationship to the phenothiazine anti-emetics and metoclopramide; it is structurally related to the neuroleptic drug droperidol. Domperidone is a dopamine antagonist in vitro; it binds strongly to the dopamine (DA) receptors of the striatal area [40]. It is felt the domperidone inhibits dopamine receptors at either the level of the anterior pituitary median eminence or at the tuberoinfundibular systems, both of which are outside the blood brain barrier. This differs significantly from metoclopramide, which inhibits dopamine (DA) centrally [9]. Domperidone is less lipid soluble, has a higher molecular weight and has lower protein binding as compared with metoclopramide [84]. These characteristics may also prevent domperidone from crossing the blood brain barrier, thus causing less extra pyramidal effects that are more commonly reported with the use of metoclopramide.

Thus, domperidone, a peripheral dopamine antagonist, may be safer than metoclopramide [39]. Drug levels of domperidone in breast milk are also significantly lower than metoclopramide (p < 0.05) [15,16]. Studies have shown that breast milk samples taken from women receiving either a 10 mg dose of domperidone or a 10 mg dose of metoclopramide contained 10.3 ng/ml of domperidone and 68.5 ng/ml of metoclopramide (p < 0.05) [16]. Domperidone has been shown to significantly increase milk production without evidence of adverse effects in the infant [15-18]. Domperidone has been shown to raise the serum prolactin level in non-lactating women from 8.1 to 110.9 ng/ml after one 20 mg dose [40]. In a double-blind placebo controlled trial, 32 mothers of full term infants experiencing failure of lactogenesis were randomized to receive either domperidone (10 mg TID) or placebo. Prolactin levels were reported as significantly higher after the 2^nd ^day of treatment in the domperidone group (p < 0.01). The mean daily milk yield was also increased significantly in the domperidone group (P < 0.01), with a corresponding higher infant weight gain [18]. In a small double blind, randomized controlled trial (n = 16), a 7 day course of domperidone (10 mg TID) given to mothers of preterm infants experiencing insufficient milk production resulted in a significantly increased milk supply (P < 0.05), low levels of drug detected in breast milk (< 0.2 mcg/kg/d) and significantly higher maternal prolactin level when compared to the placebo group [17]. No infant or maternal side effects were reported in the above trials. Both the Canadian and American Academy of Pediatrics have approved the use of domperidone for breast-feeding mothers [41].

### g. Fortification of human breast milk

Despite the numerous advantages of human breast milk, the exclusive feeding of human breast milk to premature infants has been associated with lower rates of growth, nutritional deficits, and prolonged hospital stays [42-51]. Commercial formulas for preterm infants have been designed to meet the nutritional needs of such infants but cannot provide the infant with the advantages of human milk [3-7,22-32]. Therefore, it is generally recommended that breast milk feeds for preterm infants be fortified with a commercially available human milk fortifier (HMF) [2,7,52,53]. The inadequate intake of protein, energy, calcium, and phosphorus related to unfortified breast milk has been cited as the main reason for the need for fortifiers [42-50,55-58]. Infant fortifiers provide supplemental amounts of calories, protein, vitamins, minerals and trace elements to human breast milk in order to best meet the nutritional needs of the preterm infants.

Preterm infants are born with low skeletal stores of calcium and phosphate. They have increased requirements for these minerals in order to ensure adequate postnatal skeletal growth. Poor radiological bone mineralization, rickets and fractures have been described in premature infants receiving breast alone [55,56,58]. Supplementation of calcium and phosphorous has been shown to normalize biochemical indices, serum calcium, and serum phosphorus, as well as normal urinary excretion of calcium and phosphorous [59-61]. Serum sodium levels also normalize following supplementation [57].

Protein and energy supplementation has been associated with improved rates of weight gain and better indices of protein nutritional status [49]. The Cochrane review on protein supplementation states that protein supplementation of preterm mothers milk increases short-term weight gain: weighted mean difference 3.6 g/kg/day, 95% CI 2.4 to 4.8 g/kg/day, linear growth 0.28 cm/week, 95% CI 0.18 to 0.38 cm/week, and head growth 0.15 cm/week, 95% CI 0.06 to 0.23 cm/week. Blood urea levels also increase with protein supplementation 1.0 mmol/l, 95% CI 0.8 to 2.1 mmol/l [62]. Current supplemental feeding practices are calculated based on anticipated macronutrient and electrolyte composition of preterm mother's milk that is not being augmented by medication.

### h. Breast milk composition

Human breast milk composition is widely variable both within and between breast-feeding mothers [63]. Variation in macronutrient composition can occur at various feeding times throughout the day or night and also at the beginning and end of a feed [64]. These variations have been reported to be greater in mothers of preterm infants providing expressed breast milk. Measuring samples taken from pooled 24-hour collections may limit the degree of variability reported. Variation in the composition of human breast milk has been associated with the diagnosis of either sporadic or chronic mastitis. The sodium content of the breast milk is the constituent most profoundly affected [66].

The composition of preterm mother's milk also differs from that of term mother's milk [67-69]. Although protein levels are initially higher in preterm breast milk, the natural temporal decline of protein content creates a nutritional deficit when compared to the needs of the preterm infant [5]. Studies show that there is a decline in protein content following delivery, while fat, lactose and energy content increases. These trends are more pronounced during the first 3 weeks and are greatest in the preterm group [64]. In a more recent study, random spot samples of breast milk from mothers of premature infants were analyzed to estimate macronutrient variability. Although fat content was highly variable within and between individuals, it remained fairly constant throughout lactation. Protein was less variable but was found to decrease significantly throughout the first four weeks of lactation (r = -0.45, p < 0.001), then continued to fall at a slower rate of decline over time and with increased volumes of breast milk [70]. Several studies have reported similar findings [67,70-74].

Maas [74] studied the effects of gestational age (GA), postnatal age (PNA), and post-menstrual (PMA = GA+PNA) on the macronutrient composition of very preterm mothers milk. Total nitrogen, fat, lactose and carbohydrate concentrations, energy density and 24-hour volume were determined from 282 (24 hour) samples collected (day 7–55) from seventy mothers of premature infants (25–29 weeks gestation) [74]. The major findings of the study were that developmental changes in milk composition are largely determined by PNA, minimally by GA and not at all by PMA. Milk volume (24 h) itself did not show a dependence on GA, PNA or PMA. When volume was used as a time varying covariate in the analysis, total nitrogen content decreased while lactose and carbohydrate content increased when 24-hour milk volume increased. These findings were in accordance with the literature [70,71,73].

There have been two studies examining the effect of metoclopramide on macronutrient content and sodium content of term mother's milk. When term breast milk samples from primiparous women taking metoclopramide were compared to samples from a similar group taking a placebo, the expected decline in protein content occurred at an accelerated rate in the treatment group [19]. Sodium concentration in term human breast milk was compared in a smaller study using a similar design to determine the effect of metoclopramide. No significant differences were detected between groups. The small sample size (n = 22) and lack of data regarding calcium and phosphorus levels warrant further investigation in relation to preterm milk composition [21]. Since domperidone differs in structure and mechanism of action from metoclopramide and since studies evaluating metoclopramide's effect on breast milk composition have been limited to term mother's milk, our study is both warranted and necessary to ensure optimal infant nutrition.

## Hypothesis

The macronutrient composition (protein, fat and calories) of human breast milk will be significantly altered by the administration of domperidone.

## Methods/Design

### a. Objectives

The intent of this study is to evaluate the effect of domperidone on the macronutrient composition of breast milk among mothers of preterm infants. Potential changes in protein, fat, lactose, energy, calcium, phosphorus and sodium content in expressed breast milk will be assessed. Secondary objectives include assessment of the effect of domperidone on breast milk volume, prolactin level, daily infant weight, and breastfeeding rates 2 weeks after treatment completion and at discharge.

### b. Study design

We propose to carry out a randomized double-blind placebo-controlled study comparing the effect of domperidone use on the macronutrient composition of preterm mother's milk.

### c. Study population

The source population consists of mothers of preterm infants delivered at less than 31 weeks gestational age admitted to the Neonatal Intensive Care Unit at the IWK Health Centre who are providing expressed breast milk to their infants and who experience lactational failure three weeks after delivery.

### d. Inclusion criteria

i. Mother of an infant born less than 31 weeks gestation

ii. Women mechanically expressing breast milk using a double collecting system

iii. Experiencing lactation failure indicated by at least one of the following:

A decreasing milk supply (by greater than 30 percent from peak volume based on maternal account)

An inability to provide adequate breast milk to meet the daily nutritional intake of their infant

iv. Women who have had little or no improvement in milk production following education/counseling with a lactation consultant/Neonatal Intensive Care nurse with respect to non-pharmacological techniques.

v. Postpartum period equal to or greater than three weeks.

### e. Selection criteria for study subjects

Women who meet the inclusion criteria will be approached by the study investigator/nurse, informed of the study. Signed written informed consent will be obtained.

### f. Exclusion criteria

i. Participants receiving any medication known to alter the effect of domperidone (e.g. cimetidine, ranitidine, famotidine, and nizatidine) or medication that interacts with domperidone (e.g. haloperidol, lithium).

ii. Experiencing mastitis

iii. Having a chronic or debilitating illness.

iv. Previous breast surgery

v. Having a known lactose intolerance

## Allocation of participants to the trial groups – see figure 1

**Figure 1 F1:**
[figure not shown]
Allocation of Participants to the Trial Groups.

### Randomization

Eligible and consenting woman will be randomized in blocks of four. Pharmacy staff will randomly (using a computer based code) assign mothers to receive either domperidone, 10 mg orally three times daily [17,38] or placebo for a two week period. Mothers of infants >3 but < 4 weeks postpartum will be randomized separately from those ≥ 4 weeks postpartum in order to ensure identical proportions within the domperidone and placebo groups (i.e. randomizations will be stratified by postpartum duration at study entry). Participants will receive their 2- week drug or placebo supply following enrollment. They will be provided with instruction related to self-administration and asked to return the medication vial and any unused medication at the completion of the two-week period. The study nurse/investigators will be in close contact with the mothers and review instruction related to medication on study days 4, 7, and 14.

## What are the proposed methods of protecting against sources of bias?

The double blind study design in which participants, neonatal staff, and study personnel will be blinded to group enrollment will ensure that non-domperidone related intervention effects and information collection is similar between the drug and placebo groups. In order to have similar presentation and appearance of domperidone and placebo, domperidone tablets will be crushed and mixed with lactose. The resulting powder will be placed in clear capsules. Plain lactose powder will also be placed in clear capsules to act as the placebo. Participants will receive a two-week supply of either domperidone or placebo following randomization at no cost to them. Measured prolactin levels will not be made available until the completion of the study period.

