### c. Statistical analysis

Analysis and inference will be based on the intention-to-treat principle. Efforts will be made to ensure that follow up is complete for all subjects and that there are no missing values for any of the subjects for any variable. Blinding of group assignment will be retained until after the analysis is completed. Baseline characteristics of study subjects will be contrasted to ascertain that randomization has in fact produced comparable groups with respect to all variables that effect the composition of breast milk including gestational age at delivery and duration since delivery. The primary outcome of interest will be a potential decline in breast milk protein content over time within the domperidone group versus the placebo group. This analysis will compare the means in the two groups before and after treatment and contrast the mean difference between groups using 95 percent confidence intervals and a p value. The stratified nature of the randomization will be accounted for in the analysis. If differences are noted in baseline characteristics, inferences will be made based on observed and (linear regression) adjusted differences between groups. Analysis for fat, lactose, energy, calcium, phosphorus and sodium content in expressed breast milk will be done in an identical fashion as for protein by comparing the means in the two groups before and after treatment and contrasting the mean differences between groups using 95 percent confidence intervals and a p value. Prolactin levels will be compared between the two groups and used to determine the correlation between prolactin levels and volume of milk produced.

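### Two different fills in clear capsules make product masking depend on the powders looking alike, a weakness that an opaque shell would avoid

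*Protocol article*

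**What the plan says.** The relevant text is in the protocol article, under the heading that asks how sources of bias will be guarded against. The purpose of the formulation is given first: "In order to have similar presentation and appearance of domperidone and placebo". The active product follows: "domperidone tablets will be crushed and mixed with lactose. The resulting powder will be placed in clear capsules". The placebo is described next: "Plain lactose powder will also be placed in clear capsules to act as the placebo".

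The same section names the groups to be kept unaware: "participants, neonatal staff, and study personnel will be blinded to group enrollment". It adds one further safeguard: "Measured prolactin levels will not be made available until the completion of the study period". The Statistical analysis section adds another: "Blinding of group assignment will be retained until after the analysis is completed".

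Under Randomization, pharmacy staff make the assignment from a computer code, in blocks of four within two postpartum strata. Mothers take the capsules themselves and return the vial with anything unused. The compliance section places the pill counts in pharmacy.

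**The concern.** The aim is similarity of appearance, but the two fills are not the same material. One contains a whole ground tablet, the other does not, and the shell chosen for both is transparent. Any difference in colour or texture would be open to view. An opaque shell would make the question irrelevant.

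If the products could be told apart, some of the trial's data would be exposed. Milk volume is taken from the mother's own diary. The literature review says that longer pumping contributes, with variable success, to augmenting supply, so belief about treatment could act through effort. Breastfeeding two weeks after treatment and at discharge is partly the mother's choice. Side effects are asked about by the research team on days 4, 7 and 14 (Ethics section). Withheld prolactin results and blinded analysis are useful, but neither prevents anyone from seeing a capsule.

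**Working it through.** The plan gives no figure on this point, so the check is mainly a reading of the sections side by side, with two small calculations for context.

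**1. What the two products share.** Both contain lactose and both use a clear shell. Crushing removes the tablet's shape and any marking.

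**2. What they do not share.** Only the active fill contains ground tablet. The article does not give the tablet's colour or its other ingredients, and does not say that the two powders match. It states similarity as an aim. The visible difference could therefore lie anywhere from none to obvious, and the document does not say where.

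**3. How often a capsule is seen.** The duration section gives three doses a day for 14 days. Assuming one capsule per dose, 3 × 14 = 42 capsules per woman. This counts viewings and does not measure unblinding. In a parallel-group trial each woman receives one product and has no comparator of her own.

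**4. Who could compare.** The trial runs in one neonatal unit. Most mothers are expected to visit regularly, and study staff go over the medication instructions with them on days 4, 7 and 14. Comparison between capsules is possible in that setting, but the article does not describe staff inspecting them.

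**5. A possible consequence for allocation.** Suppose staff could recognise the two powders, knew the block size and knew every earlier allocation in a stratum. In a block of two A and two B, always guessing the arm with more places left, the chance of a correct guess by position is:
- first: 1/2 = 50%
- second: 2/3 = 67%
- third: the first two agree with probability 1/3 (guess then certain) and differ with probability 2/3 (guess then 1/2), so 1/3 + 2/3 × 1/2 = 2/3 = 67%
- fourth: 100%

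The average is (1/2 + 2/3 + 2/3 + 1)/4 = 0.708, or 71%, against 50% with masking intact. This is a ceiling under stacked assumptions, not an estimate for this trial.

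**6. Which outcomes are exposed.** The Chemical analysis section has total nitrogen measured by the Kjeldahl method on pooled 24-hour milk sent to an outside centre. Knowledge of the arm on the ward has little direct way into that measurement. Diary volume, breastfeeding rates and side-effect reports have no such protection. Volume and breastfeeding rates are listed under Other outcomes.

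**The case against.** The strongest reply is that nothing here is wrong or contradictory. The plan does attend to appearance: it crushes the tablet, dilutes it with lactose, uses lactose as the placebo and puts both in the same shell. No visible difference is documented, and matching checks may well be described in a full protocol or pharmacy manual that is not shown. Most of this stands. The absence of a matching check from an article is no finding, and none is made of it. What survives is narrower: the article states its choice of shell, and that choice leaves masking dependent on a match that an opaque shell would make unnecessary.

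A reader might go further in four ways that the document does not support.

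- That the clear shell defeats the purpose of the formulation. This would need a visible difference, and the article shows none.
- That protection from bias rests wholly on the capsules. Pharmacy-held computer assignment, withheld prolactin results, a laboratory assay and blinded analysis all contribute.
- That returned vials expose blinded staff. Pill counts are done in pharmacy, which makes the assignment and is not named among the blinded groups.
- That the protein outcome is biased through pumping. The literature review does report total nitrogen falling as 24-hour volume rises, in a cited study. But the route needs a visible difference, a correct guess, a change in pumping by arm, a change in volume and then a change in protein. No step is quantified, so the route is speculative.

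**Conclusion.** The point holds as a modest, avoidable vulnerability in a stated design choice. Two different powders in transparent shells leave masking of the product dependent on their looking alike. It is not evidence that the blind failed or would fail.

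Its size cannot be given. If ground tablet and lactose cannot be told from lactose alone, the effect is nil. If they can be told apart, the exposure falls mainly on mothers or study staff able to compare capsules, and on behaviour-dependent or self-reported data. Direct bias in the assayed protein outcome is likely small in either case. The conclusion assumes only that a clear shell lets the fill be seen and that the fills are as the article describes them.

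**What to change.** In the section on protecting against bias, replace the clear capsules with identical opaque capsules in both arms, in the sentence on domperidone and in the sentence on placebo. Dose, schedule, sample size and analysis are untouched.

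The direct cost is a different empty shell in pharmacy. There is one complication. The Discussion reports first enrolment in October 2003 and seven women enrolled by the pause in June 2004. A change after that start would leave two presentations within the trial. Had it been made when enrolment resumed, 44 − 7 = 37 of the planned participants would have received the opaque form. If both arms switch on the same date for newly enrolled women, the change applies equally to drug and placebo and the comparison between arms stays balanced.
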